### Maintaining participant involvement

Due to the long study period (24 months), two strategies will be employed to keep participants engaged with the trial. Firstly, a newsletter will be sent by post at approximately 7, 14 and 21 months providing information and an update on study progress. Secondly, a prize draw will take place at the end of the 6 and 24 month follow-ups for each of the three cycles at each site. Participants will only be entered into the prize draw on return of their completed questionnaires. Participants will be informed of the prize draw when they are notified of their group allocation post randomisation.

### Fidelity assessment

We will conduct a fidelity assessment to explore the appropriateness of the facilitator training, supervision and subsequent intervention adherence. Fidelity checks will assess how well the Lifestyle Matters programme is delivered according to the intervention protocol and the published manual. Checks will adhere to an intervention fidelity framework based on that identified by the Behaviour Change Consortium and NICE guidance on behaviour change [46,47]. Table 1 provides an overview of the fidelity assessment and quality assurance parameters described by Bellg *et al.* (2004), including intervention design, training, delivery, receipt and enactment [46].

**Table 1 T1:** **Lifestyle Matters RCT fidelity assessment strategy (adapted from Bellg *****et al.***[46]**)**

	**Goal**	**Description**	**Fidelity**
Trial Design	Comparable treatment	All participants have received the same programme tailored to the needs of the group/setting.	• 16 weekly meetings will be offered to all participants with delivery of a minimum of 8.
			• Four, one-to-one meetings will be offered to all participants. Uptake and attendance recorded by the facilitator.
	Risk to implementation	Plan for potential issues that could affect the delivery of the Lifestyle Matters programme.	• A range of recruitment strategies will be implemented including GP mail-outs for each geographical area, referrals from health and social care, referrals from third sector and posters/leaflets.
			• A pre-arranged set of days and times for weekly meetings will be offered from which participants can choose.
			• Undertake three recruitment cycles in three geographically separate areas, one per cycle, to prevent saturation.
Monitoring provider training	Standardised training and facilitator skill acquisition	All facilitators receive the same training programme tailored to the group/setting.	• Observation of the training session by two researchers using a content checklist (evidence of skill transference as demonstrated through, for example, role playing activities and reflective exercises).
		All facilitators understand and engage with the intervention programme training in a similar way.	• Training delivered by the same trainer.
			• Manual and CD-Rom provided to all trainees.
			• Completion of training exercises by facilitators.
Monitoring intervention delivery	Standardised delivery	All facilitators use the same techniques and content from the programme.	• Observation using a content checklist by two researchers.
			• 75% of opportunities for completing goal setting are recorded (both for individual and group).
			• Range of materials from the Lifestyle Matters programme received by all participants.
			• Facilitators maintain reflective diaries.
			• Weekly facilitator record from group meetings.
			• Participant and facilitator semi-structured interviews.
			• All participants receive certificate of attendance/achievement.
			• Facilitators meet the NHS Band 4 equivalent job description.
	Minimise drift in skills/delivery	Adherence to training content and delivery over the three cycles of the intervention.	• Observation using a content checklist by two researchers
			• OT supervisor protocol.
			• Each facilitator will attend between 8 and 16 sessions in total of which half should be delivered face-to face.
Monitoring receipt of intervention	Participant attendance and engagement	Record the numbers of participants attending the programme each week	• Registers completed by facilitators for weekly meetings and one-to-one sessions where arranged.
		All participants take part in the group meetings and activities	• 75% of opportunities for completing goal setting are recorded (both for individual and group).
		Impact of intervention on participant in terms of well-being	• Participant and facilitator semi-structured interviews.
			• Patient Reported Outcome Measures (PROMS).

The efficacy of facilitator training and supervision will be evaluated using a number of methods. All facilitators and supervisors will receive the same two day training delivered by the same trainer. The training will be observed by two participant researchers and an observation checklist will be used to evaluate delivery and receipt of the training. A purposive selection of intervention group meetings will be video recorded at each site by the facilitators. Two researchers will then assess intervention delivery using an observation checklist based on the contents of the manualised programme and two day training. Findings from the checklists will be used to identify any areas of concern regarding failure to deliver the intervention as per the intervention protocol and manualised programme. This study recognises the complexities of balancing conducting high quality research with that of delivering an intervention in a real world setting. It is appreciated, therefore, that to maintain intervention fidelity, a level of feedback is required to help develop facilitator understanding and skills during delivery of the programme based on the findings of the fidelity assessment. One of the purposes of high level research is to highlight such inadequacies, for example, in training provision that may affect intervention fidelity, but also to ensure that study fidelity is not lost. Facilitators will be asked to complete reflective diaries and a supervisor protocol will be provided as a guidance document for those involved in supervising facilitators.

A number of tools will be used to monitor participant engagement and adherence to the Lifestyle Matters programme, including attendance registers for weekly meetings and individual one-to-one sessions. Receipt of the intervention will be monitored using participant semi-structured interviews to explore perceptions and attitudes towards the programme. We will also interview at least one intervention facilitator at both sites during the first and third cycle of the intervention to elicit their experience of the training and subsequent programme delivery.

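### Purposively selected meetings filmed by the facilitators can flag delivery problems, but cannot represent overall delivery or drift across cycles

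*Protocol article*

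**What the plan says.** The text after Table 1 in the Fidelity assessment section of the protocol article sets out how group delivery is observed: "A purposive selection of intervention group meetings will be video recorded at each site by the facilitators". It continues: "Two researchers will then assess intervention delivery using an observation checklist based on the contents of the manualised programme and two day training". So facilitators film, and researchers score.

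Three uses are given for this observation.

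- **Finding problems.** "Findings from the checklists will be used to identify any areas of concern regarding failure to deliver the intervention". The same text adds that "a level of feedback is required to help develop facilitator understanding and skills during delivery of the programme", based on what the fidelity assessment finds.
- **Judging delivery overall.** The opening of the section says: "Fidelity checks will assess how well the Lifestyle Matters programme is delivered according to the intervention protocol and the published manual". Table 1 lists checklist observation by two researchers under standardised delivery, where the standard is that every facilitator uses the same techniques and content.
- **Judging drift.** Table 1 lists the same observation under minimising drift, where the target is adherence to the training over all three cycles.

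Table 1 names other sources on delivery: "Facilitators maintain reflective diaries", "Weekly facilitator record from group meetings" and "Participant and facilitator semi-structured interviews". It also lists a protocol for the occupational therapy supervisors.

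**The concern.** The first use needs only informative sessions, and purposive selection is an accepted way to get them. The other two need more. A statement about how well the programme was delivered generalises from the filmed meetings to all meetings, groups and facilitators. A statement about drift compares cycles, so the meetings seen in each cycle must be comparable. Purposive selection secures neither property by design.

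The people being assessed also operate the camera, so they know which meetings will be scored. Scoring by two researchers guards against lenient self-rating. It does not guard against changed behaviour in a filmed meeting.

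At stake is the reading of the trial result. The programme is delivered by staff at Band 4 level after two days of training, and the Trial design section says the trial investigates implementation. If the result is null, readers will ask whether the programme failed or was poorly delivered. Observation that cannot be generalised gives a weak answer. The estimate of the treatment effect itself is not touched.

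**Working it through.** The article states no adherence figure, number of recordings or sampling fraction, so there is no figure to reproduce. Two small calculations show what the filmed meetings would have to represent, and why purposive selection leaves the answer open.

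**1. The set of meetings**

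Inputs: two sites (Trial design), three cycles and two groups per location (Participant recruitment), 16 weekly meetings offered with at least 8 delivered (Table 1).

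- Groups: 2 sites × 3 cycles × 2 groups = 12.
- Meetings if all are held: 12 × 16 = 192.
- Meetings at the stated minimum: 12 × 8 = 96.
- Plausibility check: 134 intervention participants / 12 groups = 11.2 per group, inside the range of 8 to 16 given under Intervention.

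Statements about overall delivery therefore concern roughly 96 to 192 meetings, and statements about drift compare about a third of them (32 to 64) per cycle.

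**2. What selection can do to the observed share**

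Let *p* be the true share of meetings delivered as intended, and *k* the chance that such a meeting is filmed relative to one that is not delivered as intended. The expected share among filmed meetings is

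*p·k* / (*p·k* + 1 − *p*).

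Both *p* and *k* are assumptions; the article gives neither.

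| *k* | *p* = 0.60 | *p* = 0.80 |
|---|---|---|
| 0.5 (problem meetings sought out) | 0.30/0.70 = 0.43 | 0.40/0.60 = 0.67 |
| 1 (selection unrelated to quality) | 0.60 | 0.80 |
| 1.5 | 0.90/1.30 = 0.69 | 1.20/1.40 = 0.86 |
| 2 | 1.20/1.60 = 0.75 | 1.60/1.80 = 0.89 |
| 3 (good meetings favoured) | 1.80/2.20 = 0.82 | 2.40/2.60 = 0.92 |

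The same true delivery of 60% can look like 43% or 82%. If *k* changed from 1 in one cycle to 2 in another while *p* stayed at 0.60, the observed share would move from 0.60 to 0.75 with no real change in delivery. A random draw sets *k* to 1 by design, apart from meetings that cannot be filmed.

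**3. Whether the other sources fill the gap**

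The diaries, weekly records and attendance registers are completed by the facilitators. Weekly supervision by occupational therapists is not described as observing meetings. Participant interviews are independent of the facilitators, but they record experience and cover a purposive sample of around 10% of the intervention arm (Process evaluation), or about 13 of 134 people. The videos remain the only described researcher observation of group delivery.

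**The case against.** The strongest reply is that the videos are formative quality assurance. Their stated use is to find problems and give feedback, and purposive sampling is legitimate for that. No percentage is planned from them; the one percentage in Table 1, on recording goal-setting opportunities, is not tied to the videos. This stands for the narrow use. It does not dispose of the two broader uses that the same section assigns to the observation.

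Second, purposive selection might serve drift well: only three of the nine themes are mandatory, and filming the same mandatory theme in each cycle could compare cycles better than a small random draw of mixed content. That is fair, and it is a reason to stratify by theme. The article does not commit to such matching, though its selection criteria may well be in the full protocol, and their absence from an article is no fault.

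Third, some activities take place in the wider community and may be hard to film. That also stands, and a reserve list deals with it.

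Three stronger readings are tempting and are not supported:

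- *The facilitators choose their own best meetings.* The article says that they film. It does not say who selects.
- *Delivery will be overstated.* Camera awareness makes upward bias plausible, but selection that seeks out problem meetings would push scores down. The direction is open.
- *The trial's conclusion is compromised.* The primary analysis is by intention to treat and uses no fidelity data, and the interviews and supervision give some further information on delivery.

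**Conclusion.** The point holds in a limited form. Purposively selected meetings, filmed by the facilitators being assessed, are suitable for finding delivery problems. They cannot carry a representative statement about overall delivery or about drift over three cycles. Scores may be biased, with direction and size unknown; the shares tabulated above illustrate sensitivity under assumed values and do not estimate what will happen here.

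The conclusion rests on two stated features, the purposive selection and the filming by facilitators, together with the broader aims in the same section. It does not rest on any missing detail. The primary comparison is unaffected. This is a minor improvement to a secondary activity.

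**What to change.** Have the research team draw at random the meetings used to judge overall delivery and drift. Keep the number of recordings, the two raters and the checklist as they are. Stratify the draw by site and cycle and, where numbers allow, by mandatory versus other themes, so that cycles are compared on similar content. Keep a randomly ordered reserve list for meetings that cannot be filmed, and give facilitators only short notice.

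Use any purposively chosen recordings for feedback, report them separately, and do not present them as a measure of overall adherence.

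The cost is some scheduling work and less freedom to film a particular session of interest, since the total number of recordings is unchanged. The change removes selection as a source of bias. It does not remove awareness of the camera: short notice limits preparation, but facilitators will still know when they are being filmed, and the report should say so.

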### Process evaluation

A qualitative sub-study will evaluate the impact of the Lifestyle Matters programme upon older people’s health and wellbeing and to identify factors which may mediate or moderate the effectiveness of the intervention. This will include identifying the mechanisms perceived to promote self-efficacy and resilience, evaluating the implementation of the intervention and eliciting participants’ experiences of the intervention. Semi-structured interviews will be undertaken with both participants and facilitators to explore their experience of the Lifestyle Matters intervention. Interview themes will include:

• How older people experience the programme and its delivery;

• What issues promote the effectiveness of intervention facilitation;

• The skills and competencies required to facilitate the programme;

• The barriers and facilitators to its uptake and continued use;

• The effect of the Lifestyle Matters programme on the social behaviours of older people.

All interviews lasting approximately 60 minutes will be conducted in a convenient location for the participant and audio recorded with consent. Transcripts of interviews will undergo respondent validation. This will be achieved by asking participants and facilitators to read through the transcript of their interview and comment on its accuracy. For the purposes of reporting, confidentiality will be assured by removing all identifiable or recognisable information.

Participant interviews will be conducted with a purposive sample of around 10% of participants allocated to the intervention across both sites and from all three cycles to elicit the range and nature of issues that influence their experiences of the interventions and perceived advantages and disadvantages. A sample frame will be used to identify the purposive sample which will be based on a range of characteristics, including sex, age, nationality, ethnicity, resident status, marital status, education, occupation and current levels of social and community based activity. Interviews will be conducted where possible within two weeks of attending their last group meeting.

Facilitator interviews will be conducted with at least one facilitator at each site. Because the facilitators will ideally remain the same throughout the whole study, the interviews will be conducted at the end of cycle one and cycle three. These will identify any changes in the facilitator’s experience of delivering the intervention between cycle one when they first receive and implement their training through to the third cycle when a more practiced and proficient delivery would be expected. Should there be a need for a replacement facilitator to take over a group, they will also be included in the interviews.

The following patient reported outcome measures, the Brief Resilience Scale, de Jong Gierveld Loneliness scale and the General Perceived Self Efficacy (GSE) Scale, will be used to evaluate the impact of the Lifestyle Matters programme upon resilience, self-efficacy and loneliness.

#### Analysis

Analysis of the semi-structured interviews will commence at the end of each data collection period (intervention cycle). The same methods of analysis will be applied to both the participant and facilitator interviews. Transcripts of interviews will be entered into NVivo and Framework Analysis used to examine each respondent’s data within an overall framework that is related to the intervention process. The thematic framework will be identified by two researchers and an index developed which will then be used to recode the transcripts and the data will then be charted and mapped for interpretations to develop explanations to understand the processes underlying the programme. Results will also be used to explore potential explanations for the quantitative findings and identify whether there are other emerging factors influencing uptake and impact of the intervention.

### Trial monitoring

Trial set-up and monitoring have been agreed upon with the study sponsor, the University of Sheffield. A Data Management and Monitoring Plan (DMMP) will be implemented at both sites (Sheffield and Bangor), including periodic assessment during recruitment, 6 and 24 month follow-up and study closure. Monitoring visits will include source data verification checks, data completeness checks and individual staff interviews to discuss study procedures. Additional assessments will be performed if a need is identified.

### Data management

The CTRU will undertake data management and ensure the trial is conducted according to Good Clinical Practice (GCP) Guidelines and local standard operating procedures. Data will be collected and retained in accordance with the Data Protection Act 1998. Anonymised trial data will be entered into a secure validated web based database system (Prospect) developed and hosted by the CTRU. The trial will allocate a unique screening and participant identification number to each participant. Any information provided by a participant will be handled in confidence, except where there is an issue of safety, in which the participants GP will be notified with their consent. Research participants will be protected by the removal of any recognisable, personal, confidential or sensitive data.

A requirement of the MRC LLHWB Cross-Council Programme is that primary outcome data resulting from the trial are shared with the wider research community through the UK Data Archive. Consent to share these data will be sought from participants. We will also obtain permission to share participants’ personal information with the Data Linkage Service (NHS IC), including name, address and date of birth in order to obtain regular health status reports during the period of follow-up, the purpose being, to prevent unnecessary contact with participants who may have died during this time.

### Trial oversight committees

The conduct of the trial will be overseen by three committees according to the CTRU standard operating procedures. The committees will include a Trial Management group (TMG), a Trial Steering Committee (TSC) and a Data Monitoring and Ethics Committee (DMEC). The TMG will consist of key individuals directly involved in the development and delivery of the trial including the PI, CI, Study Manager and collaborators. There will also be lay representation from an older person. The TMG will design and deliver all aspects of the trial and act on recommendations of the TSC and DMEC. The TSC will be composed of an independent chair and members with expertise in delivering RCTs and trial monitoring. The TSC will advise the CI on aspects of trial implementation, provide supervision of the trial protocol and statistical analysis plan, monitor trial progress and provide advice and consider recommendations from the DMEC. The DMEC will be composed of an independent Chair, Statistician and content expert. The DMEC is responsible for monitoring participant safety, monitoring trial results in accordance with the statistical analysis plan and providing recommendations to the TSC regarding trial continuation due to issues of ethics, safety and serious adverse events.

## Discussion

Robust and high quality research, in particular pragmatic trials in a UK setting, is required to help support service providers, health and social care managers and clinicians when making decisions about implementing evidence-based psycho-social interventions. Although Lifestyle Matters is already an established manualised programme and is being implemented sporadically in the UK by health and social care services, evidence from high level research of improved health and mental wellbeing outcomes in older people will be required before improvements in implementation will become visible. The proposed research will determine the clinical and cost effectiveness of an occupational therapy based psychosocial intervention (Lifestyle Matters) for people aged 65 years and older in a UK context, including any long term effects of sustainability.

## Trial status

Recruitment commenced on the 14 August 2012.

## Abbreviations

6CIT: Six Item Cognitive Impairment Test; AfC: Agenda for Change; BCUHB: Betsi Cadwalador University Health Board; CTRU: Sheffield Clinical Trials Research Unit; GCP: Good Clinical Practice; DMMP: Data Management and Monitoring Plan; MH: Mental health; MMSE: Mini Mental State Examination; MRC: Medical Research Council; NHS: National health service; NICE: National Institute for Health and Care Excellence; NISCHR: National Institute for Social Care and Health Research; PCRN: Primary Care Research Network; PROMs: Patient Reported Outcome Measures; QALYs: Quality Adjusted Life Years; QIPP: Quality, Productivity and Prevention; TSC: Trial Steering Committee.
